### Study population

The target population is children between the age of 3 to 17 with crouch gait from cerebral palsy (CP) or knee extension deficiency from another neuromuscular disorder, including muscular dystrophy (MD), spina bifida (SB), or incomplete spinal cord injury (iSCI). We plan to specifically target children with these diagnoses because the associated gait pathology is known to progress toward loss of ability to walk with age, often as early as puberty [45]. Participants will be pooled by diagnosis; one for CP and one for other neuromuscular disorders. This design accounts for the differences in the underlying mechanism of gait pathology; subjects with CP walk in a crouched posture due to multiple impairments, including weakness, spasticity, over active muscles, motor control deficits [46], or some combination thereof, whereas patients with MD, SB or iSCI tend to present with gait pathology as a result of muscular weakness [47–49]. Each pool will complete the same study protocol but will be analyzed separately.

A recruitment flyer detailing study inclusion criteria and general information will be distributed via the NIH list-serv as well as shared with offices of clinical care providers, physicians or physical therapists in the area or displayed throughout hospitals, physicians’ offices or rehabilitation settings. We intend to also advertise the study on appropriate social media outlets (i.e. YouTube, Facebook or Twitter) and special interest groups within those sites through the NIH Office of Patient Recruitment. We may contact previous subjects who expressed interest in returning for more research participation. All prospective patients will be contacted by phone and/or email for initial screening of basic components for inclusion prior to being invited for visit 0 to complete all components of screening for inclusion.

All potential candidates and their parent/guardian will first provide informed assent/consent for the initial screening process. Following a determination of eligibility for inclusion in the protocol, the participant and their parent/guardian will then be asked to provide informed assent/consent for participation in the study. This study will follow NIH HRPP Policy 402 to ensure we provide sufficient information in an appropriate manner to each child subject to avoid undue influence or unnecessary risk while involved in research. We will require a signed consent document by the legal parent or guardian for each participant, with an assent signature line on the consent document for children age 14–17. There will be a separate assent document for children age 8–13. Children aged 6–7 will be asked to provide verbal assent for participation while children under the age of 6 years will not be required to give verbal assent because they typically are not able to fully understand the scope of scientific research.

To be eligible to participate in this study, the following inclusion criteria must be met:

Age 3 to 17 years old.Have decreased active knee extension, from a diagnosis of cerebral palsy, muscular dystrophy, spina bifida or incomplete spinal cord injuryKnee joint passive range of motion of at least 25 degrees in the sagittal plane (knee extension/flexion) assessed with hip extended in supine position. The presence of a hamstring contracture as assessed by straight leg raising test does not limit ability to participate in the study as long as range of motion requirement is met.Ankle joint range of motion of at least 15 degrees in the sagittal plane (dorsi-plantar flexion) with the foot in neutral alignment.A measured foot-thigh angle of -15 to 30 degrees in prone position.Ability to walk at least 10 feet without stopping with or without a walking aid.

If any of the following criteria are met, the individual would be excluded from participation:

Any neurological, musculoskeletal or cardiorespiratory injury, health condition, or diagnosis other than cerebral palsy, muscular dystrophy, spina bifida, or incomplete spinal cord injury that would affect the ability to walk as directed with the robotic exoskeleton.A history of uncontrolled seizure in the past year.Pregnancy. All participants who are able to become pregnant will complete a urine test at the initial screening visit and in the case of a positive test, the participant will be excluded from participation. Further monitoring will rely on self-reporting of interruption in menstruation that would require re-testing for pregnancy at the next visit.Any acute cardiopulmonary condition which limits exercise to less than 60 minutes per session or less than 5 days per week.

Participants are free to withdraw their participation in the study at any time upon request. It is also possible for an investigator to withdraw a participant from the study intervention at their own discretion, or if the subject were to experience an adverse event or if their disease progressed to a point requiring discontinuation of study intervention. When a participant terminates participation in the study, effort will be made to complete a final evaluation visit within approximately 3 weeks of the last exoskeleton walking visit.

### Intervention and dosage

The intervention used in this study is a wearable robotic exoskeleton consisting of two custom orthotic braces, one for each limb, with each having a single actuated degree of freedom at the sagittal plane knee joint (flexion/extension direction) and a passive, adjustable joint at the ankle (Fig 3A). Each limb is powered at the knee joint and controlled by the embedded electronics and sensors which can be optimized to each participant’s gait pattern. Functional electrical stimulation (FES) can be optionally included by placing surface electrodes over the targeted muscles (knee extensors) on the lower limbs. The FES electronics are integrated with the embedded control system of the exoskeleton enabling stimulation to be synchronized with the robotically delivered torque at the knee.

**Fig 3 pone.0304087.g003:**
[figure not shown]
The NIH-Agilik exoskeleton. (A) Components of the NIH-Agilik exoskeleton, which includes orthotics customized to each user, an actuated knee joint, and a passive adjust ankle joint. (B) Example torque profiles applied over the gait cycle (heel-strike to heel-strike) for each exoskeleton operational mode.

The exoskeleton is composed of multiple parts with final assembly in our facility. A 3-dimensional digital scan of each participant’s legs is taken with a Structure Sensor Pro connected to an iPad tablet and sent to an orthotics manufacturer (Ultraflex Systems, Inc.) who fabricates the custom thermoplastic shells with attached aluminum uprights on the lateral side of the limb to which the passive ankle joint and Agilik® actuator (Bionic Power, Inc.) are mounted. The upright on the lower leg includes a height adjustment that allows the distance between the ankle and knee joint centers to be expanded by up to 3 inches to account for participant growth during the study. The orthoses, actuator, and under foot force sensitive resistor (FSR, Interlink Electronics, Westlake Village, CA) are assembled to form the robotic exoskeleton by the NIH study team.

There are three available exoskeleton control strategies (Fig 3B): one that provides synergistic assistive torque to knee extension during stance and swing phase (Assist Mode), one that applies torque to oppose knee extension during stance and swing (Resist Mode), and one that provides knee extension assistance during stance phase but resists knee extension during late swing (Interleaved Mode). Each mode can be used independently or can be paired with knee extensor FES. The ultimate intervention goal is to increase volitional function following completion of the community intervention training, so incorporating resistive training will be prioritized to aid in rehabilitation of knee extension deficiency [37, 38]. We will secondarily establish at least one assistive-only mode as an option for the participant if they cannot complete the prescribed dosage with the resistive or interleaved modes.

A baseline gait analysis walking with their usual assistive devices (i.e. AFO, walker, crutches) using motion capture and EMG, will be used to set the initial parameters of the device after fabrication, which typically takes 4–6 weeks. After this time, the participant will return to the lab for fit-testing, calibration and tuning of the exoskeleton control parameters. As part of this process, the primary exoskeleton mode will initially be set to the Resist Mode, which applies resistance to knee extension during stance and swing phase. In this tuning phase, the torque profile is customized to each participant by specifying the magnitude and ramp rate of the torque provided during each of the five gait phases (Fig 3B). If the participant is unable to ambulate in this mode, the primary mode will revert to the Interleaved Mode, which assists extension during stance and resists it during swing. Additionally, a secondary Assist Mode of operation will be set for each participant. Prior to taking the device home for the community intervention training, each participant and their caregiver must complete an up to 10 visit accommodation period for walking in the primary and secondary modes. These sessions will consist of walking overground across various surfaces and environments at the hospital, including tile, laminate and carpet indoors, as well as outdoor pathways with inclines and declines and concrete sidewalks. Clinical observation by study physical therapists, as well as analysis of exoskeleton sensor data during each type of walking, will be completed to ensure safe operation and optimal exoskeleton controller performance across the conditions and modes. The accommodation period also includes education of the participant and parent/caretaker on how to don/doff the exoskeleton, how to operate its software to turn it on/off, and how to charge the battery. The participant will be allowed to take the device into the community for 12 weeks of intervention if the user, their caregiver and the study team members are comfortable with their competency using the device. All control parameters will be set before the user takes the device home, so they will not be required to tune the device outside of the clinical setting. The participant will receive a laptop computer with software that enables the user to switch between operational modes as well as complete virtual telehealth visits with the study team. The custom software also enables the user or study team to collect sensor data from the exoskeleton during the weekly virtual visits, which will be used to verify the exoskeleton operation each week and make any changes to the controller parameters, if necessary. The participant will be instructed to utilize their primary mode for exoskeleton training, with a target of 1 hour/day for 5 days/week. They will be permitted to use the secondary Assistive Mode, if desired, after completing the primary mode training for the day, or on days when training is not prescribed. Participants are asked to complete a log of their exoskeleton use during the intervention period, including the number of minutes and mode of operation for each day. During the community intervention period the study team will set up weekly check-ins with the participant. These sessions are utilized to confirm there are not fit or operational issues with the exoskeleton and to review participant compliance with training procedures and provide encouragement to continue or enhance compliance if necessary. If any technical issues with the device were to arise, the user will be instructed to contact the study team immediately rather than wait for the weekly check-in appointment. If repairs or maintenance to the exoskeleton are necessary, the study team will travel to the participant to complete them as soon as possible.

### Study assessments and outcomes

All participants will complete the same study procedures and assessments (S1 Table), only varying in order of completion by Group (Fig 2). Each assessment visit will include collection of all outcome measures as indicated in Table 1. For Group A, assessments will be performed in the following order: at baseline (upon enrollment), initial outcome assessment (after in lab accommodation), intermediate outcome assessment (6 weeks after start of community exoskeleton intervention), final outcome assessment (12 weeks after start of community exoskeleton intervention), follow up outcome assessment (6 weeks after completing community exoskeleton intervention), and standard outcome assessment (12 weeks after starting standard therapy control). For Group B, assessments will be performed as follows: baseline assessment, standard outcome assessment, initial outcome assessment, intermediate outcome assessment, final outcome assessment, and follow up outcome assessment.

**Table 1 pone.0304087.t001:** Outcome measures by ICF domain and data collection timepoints.

Outcome Measure	ICF Domain^1^	Baseline Assessment	Exoskeleton Intervention Assessments				Standard Outcome Assessment
			Initial	Intermediate	Final	Follow-Up	
Peak knee extension (deg)	Body structure	X	X	X	X	X	X
Knee extension at initial contact (deg)	Body structure	X	X	X	X	X	X
Step length (m)	Function	X	X	X	X	X	X
Gait speed (m/s)	Function	X	X	X	X	X	X
Knee moment in stance phase (Nm)	Function	X	X	X	X	X	X
Peak activation of knee extensor (mV/mV)	Function	X	X	X	X	X	X
Mean knee extensor muscle activation (mV/mV)	Function	X	X	X	X	X	X
Gross motor function classification system (GMFCS, I-V)	Function	X	X	(X)^2^	X	X	X
Pediatric evaluation of disability inventory–computer adaptive test (PEDI-CAT, scaled 20–80)	Activity	X	X	(X)	X	X	X
Gross motor function measure (GMFM-66, scored 0–198)	Activity	X	X	(X)	X	X	X
6-minute walk test (6MWT, m)	Function	X	X	(X)	X	X	X
Timed up and go (s)	Function	X	X	(X)	X	X	X
Knee extensor spasticity (Modified Ashworth scale, 0–4)	Body structure	X	X	(X)	X	X	X
Knee extensor spasticity (Tardieu scale, deg)	Body structure	X	X	(X)	X	X	X
Knee extensor isometric strength (Nm)	Function	X	X	(X)	X	X	X
Knee flexor isometric strength (Nm)	Function	X	X	(X)	X	X	X
Quebec User Evaluation of Satisfaction with Assistive Technology 2.0 (QUEST 2.0)	Activity				X		

^1^Domains as categorized by International classification of functioning, disability and healthy children and youth version [40].

^2^() indicates assessments are optional at the indicated visit.

### Hypotheses

We hypothesize that regular use of a robotic exoskeleton in the community setting will lead to functional improvement in overground walking without the exoskeleton by (i) increasing peak knee extension angle, (ii) improving overground gait speed, and (iii) improving knee extensor (vastus lateralis and rectus femoris) muscle activation and strength. We hypothesize that these improvements will be greater than changes measured before and after the 12-week standard therapy period. We further hypothesize that community-based exoskeleton training will increase motor function and mobility, which will be assessed using clinically validated scales of activity and mobility. Finally, we hypothesize that observed functional improvements as a result of the 12-week community intervention training period will persist following completion of the training, as measured during the follow-up assessment.

### Statistical considerations

Sample size was determined from pilot data collected during a prior, in-lab protocol performed at NIH Clinical Center (#13-CC-0210) using the same exoskeleton. We used the targeted mean improvement in peak knee extension during midstance, which was approximated as 10.0 degrees, with an observed standard deviation of ± 3 degrees (n = 3) and a safety factor of 4 given the previously observed variability in response to our exoskeleton [26], resulting in a computed effect size of 0.86. At a significance level of 0.05 and 90% power we estimate that 13 participants within each subject pool is required based on power analysis for a paired t-test. We estimated about 80% of enrolled participants would complete the study through the final outcome assessment, and additionally considered 25% would complete the protocol, but elect out of the community use portion. In order to ensure 13 participants have completed the required study components, we determined at most 22 participants would need to be recruited for each subject pool, setting the maximum number of participants as 44.

Our continuous data outcomes will be summarized using descriptive statistics and presented as means with standard deviation. We will summarize our categorical data as a range with percentages. The primary endpoint, peak knee angle at midstance, will be analyzed using a per-protocol analysis to include all participants who completed at least 80% (9 weeks) of the study intervention in the community using a paired t-test between the initial and final outcome assessments. Similarly, a paired t-test will be utilized to compare change in the primary endpoint of peak knee extension with the change observed over the 12-week standard therapy block. Given the potential for carryover effects, this secondary outcome will only be assessed using data from the first intervention period from each group. We will test for normality and if not found, we will use the signed rank test instead of the paired t-test. Given the potential heterogeneity within each participant pool, we anticipate the possibility for a wide range of responses in the endpoints following the intervention. To address this potential variability, we will also perform a post-hoc linear regression analysis to assess potential effects of age, weight/height, and mobility (characterized by functional scale GMFCS I-IV) on each endpoint. We will perform an interim analysis of the primary endpoint when we have reached 50% of the estimated recruitment number to evaluate the effect and the power and revise the total enrollment number if indicated.

The same statistical procedures will be used for the secondary outcome measures and exploratory outcome measures that evaluate continuous data between multiple time points. We will report the 95% confidence intervals, in addition to the mean difference and statistical significance of that difference, for each endpoint. For the exploratory analysis of dosage effect across all four outcome assessments, we will use a repeated measures ANOVA.

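### The stated 90% power with 13 participants per pool reproduces only for a one-sided 5% test that is declared nowhere; two-sided, as the planned 95% intervals imply, it is about 81%

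*Protocol article*

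**What the plan says.** All the inputs stand in the protocol article, under Statistical considerations. The targeted mean improvement in peak knee extension is 10 degrees ("which was approximated as 10.0 degrees"). The spread is given "with an observed standard deviation of ± 3 degrees (n = 3) and a safety factor of 4". The article reports these inputs as "resulting in a computed effect size of 0.86". The size per pool then follows: "At a significance level of 0.05 and 90% power we estimate that 13 participants within each subject pool is required". The test named for this calculation is the paired t-test. Allowing for 80% completion and for 25% opting out of community use, 13 evaluable participants become at most 22 recruited per pool and 44 overall.

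The analysis paragraphs of the same section plan a paired t-test between the initial and final assessments. On reporting they say: "We will report the 95% confidence intervals, in addition to the mean difference and statistical significance of that difference, for each endpoint". They also plan an interim analysis at half of recruitment, which looks at the effect and the power and may revise enrolment.

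The Hypotheses section is worded directionally, for example "i) increasing peak knee extension angle, (ii) improving overground gait speed". Neither section says whether any test is one- or two-sided.

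**The concern.** When a plan gives a significance level of 0.05 for a t-test and says nothing more, a reader takes the test as two-sided. The 95% intervals point the same way, because a 95% interval excludes zero exactly when the two-sided 5% paired t-test rejects. On that reading, 13 participants do not give 90% power.

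If the calculation was one-sided, the sizing and the reporting run at different error rates. A primary result could then be called significant while its 95% interval includes zero.

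The figure carries weight. It sets 13, 22 and 44. The Study population section says that each pool is analysed separately, so neither pool can borrow strength from the other. The interim check of power also has no fixed reference: the same interim data could be judged adequate one-sided and inadequate two-sided.

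**Working it through.** **Inputs** (all from Statistical considerations): significance level 0.05; target power 90%; standardised effect d = 0.86; paired t-test; n = 13 evaluable per pool; completion 80%; opt-out from community use 25%.

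**Formula.** A paired t-test is a one-sample t-test on the differences. Under the alternative, the statistic follows a noncentral t distribution with n − 1 degrees of freedom and noncentrality d × √n.
- One-sided power = P(T > t[0.95; n − 1]).
- Two-sided power = P(|T| > t[0.975; n − 1]).

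**Step 1: reproduce the plan's figure.** For n = 13 the degrees of freedom are 12 and the noncentrality is 0.86 × √13 = 3.10. The one-sided critical value is 1.782, which gives power of **89.9%**. This is the stated 90%, to rounding. Strictly, n = 14 is the first size above 90% (91.9%), but that difference is trivial.

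**Step 2: the same inputs, two-sided.** The critical value rises to 2.179, which gives power of **81.2%**. The type II error is 18.8%, against the 10% implied.

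**Step 3: the size needed for 90% two-sided at d = 0.86.**

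| n | Two-sided power |
|---|---|
| 13 | 81.2% |
| 16 | 89.5% |
| 17 | 91.4% |

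So 17 evaluable per pool are needed, four more than planned.

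**Step 4: could a two-sided normal approximation explain 13?** It gives n = ((1.960 + 1.282) / 0.86)² = 14.2, which rounds up to 15, and power of 87.3% at n = 13. It yields neither 13 nor 90%, and it is not the t-test that the plan names.

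**Step 5: what this means for recruitment.** The plan's yield is 0.80 × 0.75 = 0.60. Then 13 / 0.60 = 21.7, so 22 per pool and 44 in total, as printed. For 17 evaluable, 17 / 0.60 = 28.3, so 29 per pool and 58 in total.

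**Step 6: the effect size.** The printed inputs give 10 / (3 × 4) = 0.833, not 0.86. However, a pilot SD of 2.9 prints as 3 and gives 10 / (2.9 × 4) = 0.862. At that value and n = 13, power is 90.0% one-sided and 81.4% two-sided. The 0.86 is therefore consistent with a calculation from unrounded data, and it is the value used here.

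**The case against.** The best defence is that the figure does reproduce. The hypotheses are directional and the sizing rests on a targeted improvement, so a one-sided 5% calculation would fit the intent. On that view 13 is correct and only a word is missing, which a condensed article might leave to the full protocol. Two-sided 95% intervals are sometimes reported beside a one-sided test, so they do not prove that the primary test is two-sided. It can be added that 81% is a commonly accepted power, that the study describes itself as analogous to phase I/II, that the SD from three pilot participants already carries a fourfold factor, and that the interim analysis could correct a shortfall.

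Much of this stands. A reader might infer that 13 is an arithmetic error, or that the risk of missing the target effect is definitely twice what is stated. The documents do not support either: if a one-sided test was intended, 13 is right to rounding, and the near-doubling holds only for a two-sided test.

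A reader might also infer from 10/12 = 0.833 that the effect size is wrong, and derive still lower power or a larger sample. That inference fails as well, because rounding of the SD explains the gap (step 6).

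The defence does not remove the point. A directional hypothesis does not declare a one-sided test, since two-sided tests are routinely used for such hypotheses. The article does more than leave a detail open: it prints a specific power and specific intervals, and the two do not match. The fourfold factor concerns uncertainty in the SD and does not settle sidedness. The interim check needs the sidedness fixed before it can correct anything.

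**Conclusion.** The point holds in this form: the claim of 90% power rests on an undeclared one-sided 5% test and is inconsistent with the 95% intervals planned in the same section. Under the conventional two-sided 5% test, power with 13 evaluable participants is about 81%, roughly 9 percentage points below the claim, with a type II error of about 19%. Reaching 90% would take 17 evaluable per pool.

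These figures assume the plan's own d = 0.86, normally distributed differences, and 13 evaluable participants in the pool. The shortfall is conditional on two-sided testing, which is the usual convention and the one that the intervals imply but which the article does not state. If one-sided testing was meant, the sample size stands, and the defect is the missing declaration and the mismatched intervals. The wording needs to change in either case.

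**What to change.** Choose one of two routes and state it under Statistical considerations.

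1. **Two-sided (simplest).** Keep 13 evaluable per pool and the maximum of 44. State that tests are two-sided at 0.05, and restate power as about 81% at an effect size of 0.86. The 95% intervals then match.
2. **One-sided, if that was the intent.** Declare a one-sided 5% test, keep the 90% (89.9%), and report a 90% confidence interval or a one-sided 95% bound for the tests concerned.

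In either case, use the same sidedness for the interim power check, so that any change in enrolment is judged against one definition. Printing the unrounded pilot SD (about 2.9) would let a reader reproduce 0.86; nothing more is needed there.

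The cost is a few sentences. Route 1 accepts a less favourable power figure, and route 2 accepts intervals that readers may find less familiar. Neither needs more participants. Holding 90% two-sided power instead would mean 17 evaluable and 29 recruited per pool, which the correction does not require.
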